#### 11.4.3 Secondary Analyses

For secondary outcomes, we will apply multiple regression models with adjustment on stratification variables and some prespecified variables.

- All continuous variables will be compared between the two study groups using either Student t test or Mann-Whitney nonparametric test; categorical variables will be compared using either Chi-2 test, or Fischer exact test, depending on application criteria.
- Count data (number of hyperglycemic episodes) will be compared using Poisson regression model or if data are over-dispersed, negative binomial regression models.
- Binary outcomes (protein goal achievement, caloric goal achievement) with repeated measurements will be analyzed using mixed-effects logistic regression models.
- Continuous outcomes with repeated measurements will be analysed using mixed-effects linear regression models.

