| Design:                         | 
Randomized controlled study with an intervention group, a control group; a historical control group will also be studied:
 
 
- Intervention group: Glucosafe 2 is used until the patient is discharged from the ICU or for a maximal follow-up of 15 days or when he/she starts eating (voluntary feeding). Number of patients: 71
 
- Control group: Standard care according to local ICU protocols (Geneva-HUG). The maximal follow-up is of 15 days or when he/she starts eating (voluntary feeding). Number of patients: 71.
 
- Historical control group: retrospective data from a random sample of 71 patients exposed to the standard care regarding nutrition support and glycaemic control and recruited before the beginning of the pilot study in order to minimize the “cross-over” effects and to confirm the predictive accuracy of Glucosafe2. Historical controls’ data will be retrospectively harvested from the patients’ computerized record. They will be recruited within 2 years before the trial start.
 
 |
| Inclusion / exclusion criteria: | 
Inclusion criteria:
 
All patients <math>\geq 18</math> years old admitted in adult ICU- Geneva with
 
 
• An expected length of stay <math>\geq 72</math>h
 
• At least 1 blood glucose (BG) measurement <math>\geq 10</math> mmol/l or 2 BG measurement <math>\geq 8.5</math> mmol/l
 
• Informed Consent signed by the subject/ legal representative, except for patients in the historical control group
 
 
Exclusion criteria:
 
 
• Lack of legal consent or consent withdrawn, except for patients in the historical control group
 
• Pregnant or breast feeding
 
• Diabetic ketoacidosis or hyperosmolar state
 
• Oral feeding
 
• Fulminant hepatic failure
 
• Medically contraindicated to receive rapidly acting insulin by intravenous (iv) infusion or iv injection
 
                                                                                                                                             |

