### 5.4 Safety Outcomes

Hypoglycaemia

- Overall number and percentage of mild ( $\leq 3.2$  mmol/l), and severe ( $\leq 2.2$  mmol/l) hypoglycaemic events per patient and in the study.
- Number and percentage of mild ( $\leq 3.2$  mmol/l), and severe ( $\leq 2.2$  mmol/l) hypoglycaemic events due to non-compliance (only in intervention arm)

Hyperglycaemia ( $> 8.5$  mmol/l)

- The time taken to normalize blood glucose will be the time from enrolment in the study to the time of the first of two consecutive BG measurements  $\leq 8.5$  mmol/l

- Percentage of time in the ICU with hyperglycaemia (BG > 8.5 mmol/l) before and after normalization per patient and in the cohort.
- Percentage of time in the ICU with hyperglycaemia (BG > 8.5 mmol/l) before and after normalization per patient and in the cohort due to non-compliance (only in intervention arm)
- Number of hyperglycaemic episodes after normalization per patient and in the cohort
- Number of hyperglycaemic episodes after normalization per patient and in the cohort due to non-compliance (only in intervention arm)

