#### Hyperglycemia (> 8.5 mmol/l)

- Time to normalize blood glucose (the first two consecutive values values  $\leq 8.5$  mmol/l as indicator for normalization)
  - o All the BG measurements will be reported in the eCRF with the time of the measurement. The time to normalize BG will be analysed from those data for the control and the intervention group.
- Percentage of time in the ICU with hyperglycaemia (BG > 8.5 mmol/l) before and after normalization per patient and in the cohort
  - o BG values are considered constant from one measurement to the next. Percentage of time in the ICU with hyperglycemia is defined as cumulative time with BG > 8.5 divided by the time spent in the ICU.
- Percentage of time in the ICU with hyperglycaemia (BG > 8.5 mmol/l) before and after normalization per patient and in the cohort due to non-compliance (only in intervention arm)
  - o Percentage of time with hyperglycemia will be analysed jointly with the “non-compliance” outcome.
- Number of hyperglycaemic episodes after normalization per patient and in the cohort
  - o All hyperglycaemic events will be record in the CRF. Those data will be analysed jointly with the “Time to normalize BG” outcome.
- Number of hyperglycaemic episodes after normalization per patient and in the cohort due to non-compliance (only in intervention arm)
  - o All hyperglycaemic events will be record in the CRF. Those data will be analysed jointly with the “Time to normalize BG” and the “non-compliance” outcome.

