### 11.2 Determination of Sample Size

Based on data collected routinely at the ICU between January and March 2017, the time in target was 68% (SD 21%) for patients under the standard of care. Expecting the intervention to give an improvement of 10% of time in target, we would need 71 patients in each patient group to detect give the trial a power of 80% and an alpha error of 5% (two-sided). If the patient refuses to participate afterwards or withdraws from the study for whatever reason, they will be replaced in order to have 71 per group at the end of the study.

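### The post-normalisation hyperglycaemic episode count is compared with no stated time at risk, although its clock starts at a post-randomisation event and stops at a variable time

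*Protocol*

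**What the plan says.** Section 5.4 lists among the safety outcomes "Number of hyperglycaemic episodes after normalization per patient and in the cohort". It starts the clock at normalisation: the time to normalise "will be the time from enrolment in the study to the time of the first of two consecutive BG measurements" at or below 8.5 mmol/l. The Synopsis (Outcomes) instead takes two values between 5.0 and 8.5 mmol/l as the indicator of normalisation.

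The end of observation varies. The Synopsis (Design) says "Glucosafe 2 is used until the patient is discharged from the ICU or for a maximal follow-up of 15 days", or until the patient starts eating. The control group has the same 15-day and eating limits.

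For the analysis, section 11.4.3 says "Count data (number of hyperglycemic episodes) will be compared using Poisson regression model", with negative binomial regression if the data are over-dispersed. The Synopsis (Statistical considerations) says the same. Section 9.2.4 adds of this outcome: "Those data will be analysed jointly with the “Time to normalize BG” outcome". It does not say how.

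Section 11.4.1 requires all patients to be analysed as randomised. No section says how a patient who never normalises enters the count.

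**The concern.** A count can be compared between arms without a denominator only if time at risk is the same, or is balanced by randomisation. Here it is neither fixed nor protected. It begins at a post-randomisation event that is itself a listed outcome and that better glucose control should bring forward. It ends at discharge, eating or day 15, each of which can also differ by arm. An arm that normalises sooner is observed longer for further episodes; an arm that leaves the ICU sooner is observed for less time.

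Section 4.4 frames the safety objective as fewer hypoglycaemic and hyperglycaemic episodes. This is the only count of hyperglycaemic episodes in section 5.4 that is not restricted to the intervention arm. A difference that reflects only exposure could be read as harm or benefit, or could hide a real change in rate.

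**Working it through.** **The plan's own figure.** The protocol gives no figure for episode rates, normalisation times or length of enrolment. Its only reproducible figure is the sample size for the primary outcome. Section 11.2 states that "the time in target was 68% (SD 21%) for patients under the standard of care" and continues: "Expecting the intervention to give an improvement of 10% of time in target". With 80% power and two-sided 5% alpha, n = 2 × (1.96 + 0.84)² × 21² / 10² ≈ 69.2, so 70 per group. The t-test version needs 70.2, so 71. The stated 71 reproduces and does not depend on this point.

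**Expected count ratio at equal true rates.** Let T be the enrolment time, the same in both arms, and let a and b be the times to normalisation under Glucosafe 2 and control. Expected count = rate × (T − time to normalisation), so at equal rates the ratio is (T − a)/(T − b). All values of a and b, and the intermediate T, are assumptions; 15 days (360 h) is the protocol's cap.

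| Enrolment T | a = 12 h, b = 24 h | a = 1 day, b = 2 days |
|---|---|---|
| 72 h | 60/48 = 1.25 | 48/24 = 2.00 |
| 120 h | 108/96 = 1.13 | 96/72 = 1.33 |
| 360 h | 348/336 = 1.04 | 336/312 = 1.08 |

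**Unequal enrolment.** With T₁ under Glucosafe 2 and T₀ under control, the ratio is (T₁ − a)/(T₀ − b). It equals 1 when T₀ − T₁ = b − a. With 12 h v 24 h, enrolment 12 h shorter under Glucosafe 2 cancels the effect: for T₀ = 120 h and T₁ = 108 h, (108 − 12)/(120 − 24) = 96/96 = 1. A larger difference reverses it.

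**Patients who never normalise.** If a fraction p of an arm never normalises and is entered as zero, the arm's mean count is (1 − p) times the mean among those who normalise. An assumed p of 10% lowers the mean by 10% with no benefit to anyone.

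**Simulation.** Assumptions: 71 per arm, 500 replicates, 0.5 episodes per at-risk day, patient-level over-dispersion, and exponential normalisation times with mean 0.5 day (Glucosafe 2) v 2 days (control).

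- Equal true rates, mean follow-up 5, 7 and 10 days before the 15-day cap: the ratio without an offset was 1.35, 1.24 and 1.21; with offset log(time at risk) it was 1.00 each time.
- True rate ratio 0.80, mean follow-up 7 days: 1.02 without the offset, 0.80 with it.

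I use only the ratios. Rejection rates at equal true rates stayed above 5% even with the offset (about 7% to 12%) under the simple scale correction used, so over-dispersion needs proper handling. Normalisation time was also simulated independently of episode rate, so the simulation does not test the selection that comes from analysing only patients who normalise.

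**The case against.** The strongest objection is that the missing denominator is silence, not a decision. Section 11.4.3 names a model family, and both models routinely carry an exposure term. An offset is a detail often left to a statistical analysis plan, which is not shown. Section 9.2.4 ties the count to time to normalise, section 11.4.3 mentions further prespecified covariates, and section 11.4.5 allows unsuitable methods to be replaced. So a reader might infer that a raw-count comparison has been chosen, but the protocol does not say this.

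That narrows the point without removing it. The protocol itself fixes the outcome as a number and starts its clock at a post-randomisation event. The promise of joint analysis states no exposure adjustment; section 9.2.4 uses similar wording for events due to non-compliance, where it evidently sorts which events qualify. Where the authors want a time denominator they write one: time-in-target in section 5.1, and the percentage of time with hyperglycaemia, "defined as cumulative time with BG > 8.5 divided by the time spent in the ICU", in section 9.2.4. Leaving the repair to section 11.4.5 would mean choosing it during the analysis of an unblinded trial.

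Two further objections stand. The size rests on assumed normalisation times, and the gap may be small: patients are treated under the local protocol before inclusion, so some may be at or below 8.5 mmol/l at enrolment. And failure to normalise would show in the companion outcomes, time to normalise and percentage of time above 8.5 mmol/l.

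**Conclusion.** The point holds in a limited form. As written, the comparison mixes episode rate with time at risk, and treatment can change that time. Under the assumed 12 h v 24 h, the distortion runs from 4% (15 days) to 25% (72 h). It is larger for wider gaps and could be zero or reversed if stays differ.

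Three stronger readings are not supported:

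- That the comparison is certainly biased against Glucosafe 2. Earlier discharge or eating shortens time at risk and acts the other way, so the net direction is unknown.
- That patients who never normalise are scored zero by rule. There is no rule; zero follows only if sections 5.4 and 11.4.1 are applied literally.
- That the trial's main conclusion is threatened. This is one safety outcome; the primary analysis and the 71 per group do not change.

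**What to change.** 1. In section 11.4.3, compare episode rates: Poisson regression, or negative binomial if over-dispersed, with offset log(time from normalisation to end of enrolment), adjusted for APACHE II category and diabetic status.
2. State how patients who never normalise are handled, and report their number by arm. They have no time at risk and cannot enter this rate.
3. Because that rate conditions on a post-randomisation event, and alone would depart from section 11.4.1, pair it with episodes per enrolled day in all randomised patients, counted from enrolment, with offset log(enrolment time). Read it beside the percentage of time above 8.5 mmol/l, since one unbroken episode counts once however long it lasts.
4. Reconcile the two definitions of normalisation (Synopsis: two values between 5.0 and 8.5 mmol/l; sections 5.4 and 9.2.4: two consecutive values at or below 8.5 mmol/l), so that the clock has a single start.

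The cost is a few sentences and one extra model. The times needed are already to be recorded: section 9.2.4 puts every glucose value in the eCRF with its time. The downside is slightly more analysis work.

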#### 11.4.4 Interim analyses

No interim analyses are planned.

#### 11.4.5 Deviation(s) from the original statistical plan

If the statistical methods described herein prove unsuitable during the analyses, more appropriate methods will be used. All changes in methodology will be documented in the clinical study report.

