## **6. CLINICAL INVESTIGATION DESIGN**

### **6.1 General clinical investigation design and justification of design**

This study is an unblinded randomized controlled trial that aims to evaluate the performance and the safety of a new bedside tool: GS2 in comparison to the standard of care.

Data from the historical control group will be analysed retrospectively for 71 patients hospitalized in the ICU at the same period within 2 years before the study. The historical control group is included for two reasons. The first is to be able to assess cross-over effects. These may happen in the randomized control group, if the caregiver's behaviour in this group is influenced by the caregiver's exposure to the GS2 system, when the caregiver is using the system in the intervention group.

The second reason is to confirm the predictive accuracy of GS2. As described in section 3.3.1 there are modest differences between the prediction errors estimated from the three patient cohorts previously analysed with Glucosafe. It is therefore appropriate to confirm that the prediction error of GS2 is similar or smaller compared to Glucosafe's. In case the prediction error is smaller, it will be possible to reduce the frequency of blood glucose measurements, as described in IB 2.5 "Mechanisms of action". The frequency of blood glucose measurements is one of the outcomes for workload (section 9.2.3). This reduces workload and the amount of blood drawn from the patient. In case the prediction error is larger, it is a reason for discontinuation or modifications of the intervention, as noted in Section 2.9.

The analysis of data from the historical control group will start as soon as the authorization of the study has been obtained. Enrolment for the intervention and control groups will start when the retrospective analysis of the historical control group has been completed. Enrolment is expected to take 8 months. The data and the results will then be analysed and submitted for publication.

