### **6.2 Methods for minimising bias**

#### **6.2.1 Randomisation**

Randomization (1:1) will be stratified by the gravity score APACHE II (mild/moderate/severe) and by the diabetic status (diabetes/non diabetic patients). A randomization list using block randomization with variable blocks size 2, 4, or 6 will be computer-generated by an independent statistician.

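### Section 11.4.5 lets the primary method be replaced during the analysis of an unblinded trial, so the 5% error rate is not protected against a data-driven switch

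*Protocol*

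**What the plan says.** Section 11.4.5 of the Protocol reads: "If the statistical methods described herein prove unsuitable during the analyses, more appropriate methods will be used". Its second and last sentence requires changes of methodology to be documented in the clinical study report.

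The methods it refers to are those of section 11, so they include section 11.4.2. That section first names a t test or, for non-normal data, a Mann-Whitney test. It then says the primary analysis is a linear regression adjusted for APACHE II category and diabetic status. Superiority is concluded at p < 0.05. Section 11.2 sets a two-sided alpha of 5% and 80% power.

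Section 6.1 states: "This study is an unblinded randomized controlled trial". Section 6.2.2 marks blinding procedures as not applicable. The Protocol describes no blinded analyst and no blinded data review.

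**The concern.** The clause has three features that together leave the decision rule open.

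- It operates while the analysis is under way, when arm and outcome are both in the analyst's hands.
- The new method takes the place of the planned one; it is not reported beside it.
- It does not say what counts as unsuitable, who decides, or that the planned analysis remains primary.

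A method chosen after the comparison has been seen no longer has the stated error rate, and disclosing the change does not restore it. Section 2.6 declares a commercial interest of the manufacturer, which makes a rule fixed in advance more valuable.

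This is distinct from the unclear choice among named tests in 11.4.2. If 11.4.2 were repaired alone, 11.4.5 would still allow the repaired test to be exchanged for one that appears nowhere in the plan.

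**Working it through.** **1. The plan's own figure.** Inputs from section 11.2: "the time in target was 68% (SD 21%) for patients under the standard of care"; an improvement of 10%, read as 10 percentage points; two-sided alpha 5%; power 80%; stated result 71 per group.

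n = 2 × (1.96 + 0.8416)² × 21² / 10² = 2 × 7.849 × 4.41 = 69.2, so 70 by the normal approximation. The t-test solution is 70.2, rounded up to 71. Power at 71 per arm is 81.0% (normal) or 80.4% (t). The stated size reproduces. A relative 10% (6.8 points) would need 150, so the absolute reading is the one the plan used.

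**2. Null simulation.** 10,000 trials per scenario, 71 per arm, no treatment effect. Time in target is drawn from a beta distribution with mean 0.68 and SD 0.21: 0.68 × 0.32 / 0.21² − 1 = 3.934, giving shape parameters 2.675 and 1.259. Assumptions not in the documents: the beta shape, equal APACHE II thirds, 30% diabetics, and strata explaining 0, 10 or 30% of the variance on a latent scale. The Monte Carlo standard error is about 0.25 points. Where several methods are listed, the smallest p-value is always taken.

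| Two-sided type I error | R² 0 | R² 0.1 | R² 0.3 |
|---|---|---|---|
| Adjusted regression alone | 4.7% | 5.2% | 4.8% |
| Best of regression and t test | 5.4% | 6.7% | 7.1% |
| Best of the three tests named in 11.4.2 | 6.2% | 7.5% | 8.0% |
| Adding logit and rank models (only via 11.4.5) | 7.2% | 8.7% | 9.6% |

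**3. Share due to 11.4.5.** The last row minus the one above: 7.2 − 6.2 = 1.0; 8.7 − 7.5 = 1.2; 9.6 − 8.0 = 1.6 points. A separate run of 12,000 null trials that adds only a logit-transformed t test moves 6.6% to 7.4%, or 0.8 points.

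**4. Check on allocation.** The runs above do not block within strata, whereas section 6.2.1 does (blocks of 2, 4 or 6). Repeating them with such blocks, for R² 0, 0.1 and 0.3, gives 5.9%, 5.8% and 5.2% for the three named tests, and 6.8%, 7.3% and 7.2% with the two added models. Balance on the strata makes the unadjusted tests conservative, so the share due to the named tests falls. The addition from 11.4.5 stays at about 1 to 2 points. The table is therefore an upper bound in this respect too.

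**5. Direction.** Superiority is claimed only in one direction. By symmetry, false superiority is half of each figure: 3.1 to 4.0% for the named tests and 3.6 to 4.8% with the added models, against a nominal 2.5%. The relative inflation is the same.

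**6. Does the shape of the outcome force a change?** (100 − 68)/21 = 1.52, so a normal curve would put about 6% of control patients above 100%. At a mean of 78%, (100 − 78)/21 = 1.05 and about 15%. The outcome is plainly not normal. Even so, the regression alone keeps 4.7 to 5.2% (first row).

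**The case against.** The strongest reply is that most of the inflation does not come from this clause. The 6 to 8% arises from tests that 11.4.2 already names and would remain if 11.4.5 were deleted. That stands, and it limits the clause's own share to about 1 to 1.6 points.

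The clause also requires unsuitability and disclosure, whereas the simulation takes the smallest p-value every time. This stands too: the figures are bounds, not forecasts, and nothing in the Protocol suggests that misuse is intended.

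A reader might infer an error rate near 10% or above. Adding a split at 70% time in target gives 9.3 to 11.5% in the unblocked runs. The documents do not support using that figure: a split changes the outcome, not the statistical method, and the cut-point appears nowhere in the Protocol. Treating three tests as independent (1 − 0.95³ = 14.3%) overstates the effect as well, because the tests are highly correlated.

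A reader might also infer that a bounded, skewed outcome will always make the planned model arguably unsuitable. It will not: the regression holds its level at 71 per arm, and 11.4.2 already names a test for non-normal data.

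Other controls exist. Section 2.10 requires approval of substantial amendments, and section 2.11 bars deviations. But 11.4.5 is itself part of the approved plan and does not refer to them, so a switched test could be presented as compliant. A statistical analysis plan, not shown here, may set lock dates and fallbacks, and their absence from the Protocol is not the complaint. The complaint is that the Protocol states a permissive rule and does not defer to such a plan.

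**Conclusion.** The point holds as a matter of what the text permits. Section 11.4.5 authorises replacing the primary analysis with the arms in view, and documentation alone does not keep the 5% two-sided rate.

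The size is modest. The worst-case bound is about 6 to 8% from the tests named in 11.4.2, lower when stratified blocks are modelled, plus about 1 to 1.6 points from methods that only 11.4.5 admits. These figures rest on a beta-shaped outcome, assumed strata effects and selection of the smallest p-value in every trial. The sample size is unaffected, and the planned adjusted regression needs no replacement on grounds of skewness. The change is worth making because it removes a source of bias at almost no cost.

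**What to change.** Replace the clause in 11.4.5 with:

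*The primary analysis may be changed only by a documented amendment (section 2.10) made before database lock and before the primary outcome has been compared between the randomised arms. After that the planned adjusted linear regression is reported as primary and decides superiority; any alternative method is reported as a sensitivity analysis labelled post hoc.*

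The restriction should refer to the primary outcome in the randomised arms, not to any outcome. Sections 1.6 and 2.9 count severe hypoglycaemia in the intervention group during the trial, and section 6.1 analyses the historical group before enrolment. A wider wording could close the window for legitimate changes too early.

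Make this change together with naming a single primary test in 11.4.2; neither repair is sufficient alone.

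Cost: two sentences. The sponsor gives up replacing the primary test after seeing the comparison but keeps the freedom to add sensitivity analyses. The number of patients and the conduct of the trial do not change.
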